**Table 1: Summary Form of Health Status Survey (SF-36) scoring criteria**

| **8 dimensions + overall** | **Items** | **Scoring methods for each dimension** |
| --- | --- | --- |
| 1. Physiological Function(PF) | 3.1-3.10 | PF=[(actual score - 10) /20] x 100 |
| 2. Physiological Function(RP) | 4.1-4.4 | RP=[(actual score -4) /4] x 100 |
| 3. Body pain (BP) | 7,8 | BP=[(actual score -2) /9] x 100 |
| 4. Overall Health (GH) | 1, 11.1- 11.4 | GH=[(actual score -5) /20] x 100 |
| 5 Vitality (VT) | 9.1, 9.5, 9.7, 9.9 | VT=[(actual score -4) /20] x 100 |
| 6. Social Function (SF) | 6,10 | SF=[(actual score -2) /9] x 100 |
| 7. Emotional Function(RE) | 5.1-5.3 | RE=[(actual score -3) /3] x 100 |
| 8. Mental Health(MH) | 9.2, 9.3, 9.4, 9.6, 9.8 | MH=[(actual score -5) /25] x 100 |
| Overall: Health Change(HT) | 2 | HT=[(actual score - 1) /4] x 100 |

* Total Body Health measures (PCS) include: PF, RP, BP, GH;

* Total Measure of mental Health (MCS) includes: VT, SF, RE, MH.

* Scoring method for each dimension = (actual score - lowest score)/(highest score - lowest score)×100

* Actual score (for each dimension) = Add the scores for each item

Analysis of safety

Safety evaluation is analyzed on SS populations.

Proportion of antiarrhythmic drugs using within 90 days after radiofrequency ablation will be described in each group using frequencies and percentages. The range of antiarrhythmic drugs within 90 days after radiofrequency ablation was defined as the start date of ATC3 drugs between the day of radiofrequency ablation and the 90^th^ day of surgery.

Proportion of adverse events, severe adverse events, adverse reactions, and severe adverse events will be described in each group using frequencies and percentages. If necessary, changes of the laboratory and electrocardiogram variables will be analyzed before and after treatment.

Additional analysis

Additional analyses will be performed to compare primary and secondary endpoints between randomization groups after excluding patients who were still using antiarrhythmic drugs after 90days after radiofrequency ablation. Analysis methods for primary and secondary endpoints analysis described previously will be performed.

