### Secondary efficacy endpoints

(1) Changes in atrial fibrillation load at 3 months, 6 months, and 1 year after treatment. Atrial fibrillation load was defined as the longest duration of atrial fibrillation episodes, the number of episodes of atrial fibrillation, and the percentage of time patients were in atrial fibrillation during a given monitoring period.

(2) Time of first occurrence of atrial flutter/atrial fibrillation.

(3) Incidence of electrical cardioversion within 1 year after treatment.

(4) Changes of transthoracic echocardiographic indexes at 1 year after treatment.

(5) Incidence of stroke and thromboembolism at 6 months and 1 year after treatment.

(6) Health Survey Summary Form (SF-36) score within 1 year after treatment.

Safety endpoints

(1) Adverse events (AEs): Any adverse medical events occurring between the time subjects signed the informed consent and were enrolled in the study and the last follow -up, regardless of whether there was a causal relationship with the study drug, was considered an adverse event. The sum of "definitely relevant", "possibly relevant" and "unascertainable" associated with the study drug was the adverse reactions (ADRs) of the study drug, and the incidence of adverse reaction was calculated accordingly.

(2) Laboratory indicators: blood routine, urine routine, stool routine, biochemical examination and coagulation function examination;

(3) Clinical physical examination and vitals.

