# Processing of missing data

In this study, survival analysis was used to analyse the 1-year recurrence of atrial fibrillation for the primary efficacy endpoint. mITT and PPS were both included for the patients who failed to complete the 1-year follow-up due to half-way drop out or missing follow-up. The endpoint was defined as censored in the statistical analysis, and the censored date was the last follow-up date. No carry-over of missing data or multiple fillings of missing data were performed.

Missing data of secondary endpoints and safety endpoints, no filling or other processing is carried out.

Handling of dates: When only part of the date is known, the following rules are used to calculate the duration. If the start time (such as the date of first onset of AF or the date of diagnosis) is partially missing and only the day is missing, then fill in the first day of the corresponding month. If the end date is partially missing and only the day is missing, replace it with the last day of the month. If both the day and month of the date are missing, this date is treated as missing.

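### SF-36 scoring in Table 1 works only for fully answered dimensions, and the ban on processing missing secondary data means that one skipped item discards the dimension or, if partial sums are used, mis-scores it.

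*SAP*

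**What the plan says.** SAP section 3.1.2 lists as its sixth secondary efficacy endpoint "Health Survey Summary Form (SF-36) score within 1 year after treatment". Section 6.4 compares each dimension between arms by t-test or Wilcoxon rank sum test and gives the scoring in Table 1.

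The input to each dimension is defined in a note to Table 1: "Actual score (for each dimension) = Add the scores for each item". The transformation is "Scoring method for each dimension = (actual score - lowest score)/(highest score - lowest score)×100", with the numbers fixed per dimension, for example "PF=[(actual score - 10) /20] x 100" and "RP=[(actual score -4) /4] x 100". Table 1 has no rule for a dimension with a skipped item.

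Section 5 states the rule for missing data: "Missing data of secondary endpoints and safety endpoints, no filling or other processing is carried out". It makes no exception for questionnaire items.

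**The concern.** In all eight multi-item dimensions, the lowest score subtracted in Table 1 equals the number of items. The formula therefore assumes that every item contributes at least 1. With a blank, the analyst has two options, and the SAP does not say which applies:

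- **Set the dimension to missing.** A patient who answered nine of ten PF items drops out of the PF comparison at that visit.
- **Add the items that are present.** The blank then enters as 0, below the lowest possible answer, while the formula still subtracts and divides as if the form were complete.

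The first option loses information that the patient supplied. The second produces wrong scores, some outside the 0–100 scale. In SAS, the named software, the SUM function skips missing values while the + operator returns missing, so two programmers following the same text could obtain different results.

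**Working it through.** **Inputs.** Items per dimension, lowest score and range come from Table 1 and are taken as given. The SAP does not give item response ranges, so they are inferred. Since the lowest total equals the item count k, each item starts at 1, and the item maximum is 1 + range/k if the items of a dimension share one maximum. For BP and SF (two items, range 9) the maxima sum to 11 and must be unequal; 5 and 6 are assumed.

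**Complete forms.** The SAP gives no figure for a skipped item, so the only check of its own numbers is that the formulas run from 0 to 100 when all items are answered. For PF: (10 − 10)/20 × 100 = 0 and (30 − 10)/20 × 100 = 100.

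**Partial sum.** If an item whose answer would have been s is left out, the score falls by 100 × s/range. If all other answers are the lowest, the score is −100/range.

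| Dimension | Items | Lowest / range | Implied item maximum | Fall if s = 1 | Fall if s = maximum | All others lowest, one blank |
|---|---|---|---|---|---|---|
| PF | 10 | 10 / 20 | 3 | 5 | 15 | −5 |
| RP | 4 | 4 / 4 | 2 | 25 | 50 | −25 |
| BP | 2 | 2 / 9 | 5 and 6 (assumed) | 11 | 56 or 67 | −11 |
| GH | 5 | 5 / 20 | 5 | 5 | 25 | −5 |
| VT | 4 | 4 / 20 | 6 | 5 | 30 | −5 |
| SF | 2 | 2 / 9 | 5 and 6 (assumed) | 11 | 56 or 67 | −11 |
| RE | 3 | 3 / 3 | 2 | 33 | 67 | −33 |
| MH | 5 | 5 / 25 | 6 | 4 | 24 | −4 |

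Over all dimensions and answers, the fall runs from 4 points (MH, s = 1) to 67 points (RE, s = 2: 100 × 2/3). The 67 does not depend on the assumption for BP and SF. HT is a single item, so a skip simply leaves it missing.

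**Dimension set to missing.** The SAP gives no item non-response rate. Assume a rate r of 0.5–3% per item, independent between items. The share of forms that lose a dimension of k items is 1 − (1 − r)^k:

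- PF, k = 10: 1 − 0.995^10 = 4.9% to 1 − 0.97^10 = 26.3%.
- GH and MH, k = 5: 1 − 0.995^5 = 2.5% to 1 − 0.97^5 = 14.1%.
- BP and SF, k = 2: 1 − 0.995^2 = 1.0% to 1 − 0.97^2 = 5.9%.

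If blanks cluster in the same forms, fewer forms are affected.

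**Check on the remedy.** Replacing a blank by the mean of the answered items works where the items share one scale. It fails for BP and SF. With maxima 5 and 6, an answer of 6 and the other item blank gives (6 + 6 − 2)/9 × 100 = 111. An answer of 5 on the other item, with the 6-point item blank, gives (5 + 5 − 2)/9 × 100 = 89 where 100 is expected.

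**The case against.** The strongest reply is that the SAP has made a choice. Adding the scores of each item means all items, and entering a blank as 0 would itself be a form of filling, which section 5 excludes. Read together, the two passages make an incomplete dimension missing and the comparison an available-case one. That is coherent, and the negative scores would not occur. This largely stands: it is the more natural reading. But the SAP does not state it, and under it the plan still discards nearly complete answers that a simple rule would keep.

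Three stronger readings are tempting and are not supported:

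- A reader might infer that one skipped question always costs at least 15 points. Fifteen is the largest fall in PF; a low answer left blank can cost as little as 4.
- A reader might combine all 35 items of the eight dimensions and infer that 16–66% of forms are damaged (1 − 0.995^35 to 1 − 0.97^35). Section 6.4 compares the dimensions separately, so no planned test loses that share.
- A reader might infer that the arm comparison is biased because sicker patients skip more items. In a randomized, double-blind trial, symptom-related skipping that is equal in both arms creates no arm difference when treatment has no effect. Bias needs skipping that differs by arm, or a treatment effect on what drives skipping.

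**Conclusion.** The point holds as a scoring rule that gives a worse result than an easily available alternative. On the natural reading, the consequence is lost precision. The illustrative loss rates rest on an assumed 0.5–3% item non-response and on independence between items, neither of which comes from the SAP. On the partial-sum reading, the falls of 4 to 67 points and the scores below 0 follow from Table 1, with item ranges inferred as shown. Which reading would be programmed cannot be told from the text. Only a secondary endpoint is affected; the primary analysis and the sample size are not. It is worth correcting before the data are scored.

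**What to change.** Make an exception in section 5 for SF-36 items, and repeat it under Table 1:

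- If at least half the items of a dimension are answered, replace each blank by that patient's mean of the answered items in the dimension, then apply the Table 1 formula. Otherwise set the dimension to missing.
- For BP and SF, put the two items on a common scale first, or set the dimension to missing if either is blank. On a common scale, the answered item is expressed as a fraction of its own range and that fraction is applied to the blank item. With maxima 5 and 6, a top answer of 6 then gives 5 for the blank and (6 + 5 − 2)/9 × 100 = 100.
- Never enter a partial sum into a fixed-range formula.
- Report the number of affected forms per arm and dimension.

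If the sponsor prefers no imputation, the minimum is one sentence stating that a dimension with any blank item is missing.

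The cost is a few sentences and a few lines of code. The downside is a modest within-patient imputation on a secondary endpoint where the plan now has none.
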